### Study settings

The study is a parallel, double-blind, randomized controlled trial. Participants for this trial will be recruited from the communities of Shahrasti and Chandpur, Bangladesh, where arsenic levels in tube well water frequently exceed the national standard of 50 ppb. Families in these rural areas typically have their own tube well in the yard from which they collect their drinking and cooking water. Entire families will be recruited.

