#### Justification for eligibility criteria

The national standard for arsenic in drinking water is 50 ppb. To increase the possibility of detecting clinical differences between the two treatments, we chose families with wells having arsenic levels above the national standard and ≥100 ppb. Moreover, after testing all the tube wells of potential participants, we identified only 10 out of 118 wells that had arsenic levels between 50 and 100 ppb. This resulted in a small sample size for this subgroup, which may not produce interpretable results and could weaken the statistical power of the whole trial.

We planned to include children of ages 10–17 in the trial, as they are a vulnerable group and actively developing, especially those from ages 10 to 14. The observation of changes in nutritional status in these children due to lentil consumption would be especially valuable in our opinion. However, the Ethics Review Committee at icddr,b stipulated that children under the age of 14 be excluded from the study. Nevertheless, all family members of study participants, including young children, will eat the high-selenium or control lentils.

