### Sample size

We determined the sample size for this trial with an online power and sample size calculator (www.powerandsamplesize.com), based on a one-sided effect for arsenic concentration in hair.

Based on a previous intervention trial [28], in which arsenic-exposed participants received selenium-enriched yeast (100–200 μg/day, an amount two to four times higher than our dietary treatments), we calculated the sample size from their data generated after a 9-month intervention. Using the mean arsenic levels in hair of the control and selenium-treatment groups, Mean_A_ = 2.01 μg/g (±1.4) and Mean_B_ = 1.23 (±0.73), respectively, and a type I error of 0.05 and a power of 0.80, we calculated a minimum participant number of 26 per treatment group. This sample size underestimates our needed sample size due to substantial differences from our planned trial. Considering the up to fourfold lower selenium treatment in our trial, we felt it was prudent to quadruple the number (=100) and then double it to accommodate our larger age range, shorter duration, and loss to follow-up, arriving at the final participant number of 200.

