### Randomization and blinding

This trial will be double-blinded. High- and low-selenium lentils have been packed in color-coded bags (green and white), and neither the study participants nor the study investigators know of the lentil type.

Related families commonly live in the same Bari (group of homes on one plot of land) in rural Bangladesh, with families, defined as members taking meals from the same cooking pot, living in individual homes or households (HHs) in the Bari. All family members in an HH will receive the same lentil type. However, within each Bari individual HHs may receive different lentil types. Once families are recruited, they will be assigned to treatment group A or B (deficient or high-selenium lentil groups) using a computer-generated block randomization method, and one group will be randomly assigned to receive selenium-rich lentils. The sample size is 200 individuals per group. Typically a family consists of four to eight members. Thus, if there are six members per HH, there will be approximately 34 HH per group. For the block randomization we may consider blocks of variable length, e.g., four or six HHs per block; thus, in each block there will be four or six HHs. Equal numbers of HHs are distributed in the two groups, and either group may receive the selenium-rich lentils. All HHs will receive their supply of lentils weekly. Sequential numbers will be allocated to the participants, e.g., 010101, 010102 (Bari 01, HH 01, family member 01, 02, 03…), etc.

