### Data analysis

Data are stored in a password-protected database at icddr,b, through a platform that allows sharing of data between project investigators (PIs) at icddr,b and the University of Calgary. Statistical analyses will be done using the statistical software SPSS for Windows PASW version 20. Normality and homogeneity of variances will be determined. Data not normally distributed will be transformed as necessary. Initially Spearman’s correlation analyses will evaluate univariate association between arsenic exposure (urinary and hair arsenic) and outcome variables (oxidative stress, antioxidant status, lung inflammatory status, and genetic variables). Covariates (e.g., demographic and socioeconomic variables, morbidity, daily diet, and BMI of participants) will be evaluated for significant association with exposure and outcomes. Missing data are excluded from that specific analysis. Significantly correlated variables will be further analyzed in multiple linear regression models controlling for potential confounding variables stratified by sex. Potential confounders will be identified based on correlations (*p* < 0.15) with the exposure (toxic metal) and outcomes and will be included in the final models when they change the effect estimate for metal exposure on the outcome by 5 % or more.

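### Household well arsenic is known before allocation but is neither a stratum nor a fixed covariate; pre-specifying it with the baseline marker would gain precision and credibility at almost no cost

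*Protocol article*

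**What the plan says.** **Well testing.** Study settings describes the well as a household exposure: "Families in these rural areas typically have their own tube well in the yard from which they collect their drinking and cooking water". Justification for eligibility criteria shows that the values, in ppb, were in hand before enrolment: "after testing all the tube wells of potential participants, we identified only 10 out of 118 wells that had arsenic levels between 50 and 100". The only stated use of the value is the 100 ppb entry threshold, and no upper limit is given.

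**Allocation.** Randomization and blinding assigns whole households, all members receiving one lentil type. It gives about 34 households per group at six members each; the Abstract's figure of about 80 families implies 40 per group. On method it says "For the block randomization we may consider blocks of variable length, e.g., four or six HHs per block". No stratification factor appears.

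**Analysis.** Data analysis gives an open list of examples, "Covariates (e.g., demographic and socioeconomic variables, morbidity, daily diet, and BMI of participants", which does not mention well arsenic. A candidate confounder is kept if it correlates at p < 0.15 and changes the estimated effect of metal exposure on the outcome by at least 5%. Exposure there means urinary and hair arsenic.

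**The concern.** Arsenic in urine, feces and hair is the primary outcome, and drinking water is an obvious source of it. The article itself treats well level as relevant: it restricts entry to wells at or above 100 ppb to make differences easier to detect. It then makes no use of the variation above that threshold.

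Household members share both the well and the lentil type. A chance difference in well arsenic between arms therefore averages out over 34 to 40 units per arm, not over 200 individuals.

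The stated covariate rule does not reliably help. It is judged on the metal-outcome estimate, not on the lentil-arm estimate, and its exposure variables are themselves trial outcomes. Whether well arsenic or baseline arsenic enters the arm comparison is thus left to the data. At stake are the precision of that comparison and how readily a modest difference on one marker would be believed.

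**Working it through.** **1. The plan's own figure.** Sample size works "based on a one-sided effect for arsenic concentration in hair", from "Mean_A_ = 2.01 μg/g (±1.4) and Mean_B_ = 1.23 (±0.73), respectively".
- n = (1.4² + 0.73²) × ((1.645 + 0.842)/0.78)² = 2.4929 × 10.16 = 25.3, rounded up to 26. This agrees with "a type I error of 0.05 and a power of 0.80, we calculated a minimum participant number of 26 per treatment group".

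**2. Effect benchmarks.** The article states no target difference for this trial, so a range is needed.
- Pooled SD = √(2.4929/2) = 1.116 μg/g.
- Published effect: 0.78/1.116 = 0.70 SD, or 0.78/2.01 = 39% of the control mean.
- Halved: 0.35 SD (19%). This is what quadrupling the number implies, since n varies as 1/effect².
- Quartered: 0.175 SD (10%). This is a proportional reading of the up to fourfold lower selenium intake: "Considering the up to fourfold lower selenium treatment in our trial, we felt it was prudent to quadruple the number (=100").
- Detectable with 200 per arm, one-sided and ignoring clustering: (1.645 + 0.842) × √(2/200) = 0.25 SD.

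**3. Chance imbalance in well arsenic.** With m households per arm, the SD of the difference in arm means is √(2/m) between-household SDs.

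| Households per arm | SD of imbalance | 95% limit (1.96 × SD) |
|---|---|---|
| 34 | 0.243 | 0.475 |
| 40 | 0.224 | 0.438 |

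**4. Shift in the outcome.** If well arsenic correlates r with hair arsenic, the shift is r times the imbalance, in outcome SDs. The documents give no r, so these values are assumptions. With 34 per arm:

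| Assumed r | One-SD shift | 95% limit | Chance of reaching 0.175 SD, either direction | Chance of reaching 0.35 SD |
|---|---|---|---|---|
| 0.3 | 0.07 | 0.14 | 2% | 0% |
| 0.5 | 0.12 | 0.24 | 15% | 0.4% |
| 0.7 | 0.17 | 0.33 | 30% | 4% |

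With 40 per arm, the 95% limits are 0.13, 0.22 and 0.31 SD. The 95% limit equals the quartered effect at r = 0.175/0.475 = 0.37 (34 per arm) or 0.175/0.438 = 0.40 (40 per arm). With 34 per arm it equals the halved effect at r of about 0.73.

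**5. What stratifying would do.** A simulation used 68 households, blocks of four or six, normally distributed well values and 6,000 runs. The SD of the imbalance was 0.246 well SDs without strata and 0.151 with two, a fall of 39%. The 95% limit fell from 0.49 to 0.30.

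**6. What adjustment would do.** If well arsenic correlates 0.5 with the household mean of the marker (an assumption), adjusting for it alone removes 0.5² = 25% of the between-household variance. That figure assumes no adjustment for the baseline marker.

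**The case against.** Several points against this concern stand.

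- **Blocking without strata is a valid design.** Chance imbalance in a prognostic factor is not bias, and a standard error computed at household level allows for it. A reader might infer that the trial's result would be systematically wrong; the article does not support that.
- **A common shift does not mimic the hypothesis.** Trial objectives predicts higher arsenic in urine and/or feces but lower arsenic in hair. An arm with more well arsenic would tend to show more in all of them, so one marker would move with the hypothesis and another against it. A single marker could still mislead.
- **A typical imbalance need not equal the effect sought.** That reading requires the quartered effect, which the article does not state, and hair arsenic fully proportional to well arsenic, which it does not claim. At r = 0.5 a one-SD imbalance shifts hair arsenic by 0.12 SD, short of even the quartered 0.175 SD.
- **Well water is not called the main driver.** Background names irrigated rice as a further source. No distribution of well arsenic is given.
- **Adjustment is not excluded.** The covariate list is open, and baseline hair and urine are collected. Baseline values should carry much of a household's past exposure, so well arsenic probably adds less than the 25% in step 6.
- **Stratification may come too late.** Table 1 gives a start date of September 28, 2015, and recruitment is under way.

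What survives is narrower. The article does state a rule for choosing covariates, and that rule is aimed at a different estimate from the arm comparison. This goes beyond detail left to an analysis plan.

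**Conclusion.** The concern holds as an inexpensive improvement, not as an error that invalidates the design. A household-level value available before allocation is used only for eligibility, and the stated covariate rule guarantees neither it nor the baseline marker a place in the arm comparison.

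Chance imbalance could match a strongly diluted effect on a single marker, but only if the well-hair correlation is about 0.4 or more. Matching the halved effect is unlikely even at r = 0.7 (4%), and the published 0.70 SD effect is out of reach at the correlations considered. These conclusions rest on assumed correlations, 34 to 40 households per arm of similar size, and benchmarks derived from the published effect because the article gives no target of its own.

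**What to change.** In Data analysis, define the comparison of arms as a pre-specified model. Its fixed covariates should be log well arsenic at entry and the baseline value of the same arsenic marker. For these two terms, drop selection by p-value and change in estimate.

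For households not yet allocated, the blocks in Randomization and blinding may also be run within two strata, below and above the median well arsenic of eligible households. Where allocation has already been made, keep it and apply the covariates only.

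The cost is two terms in the model and, if stratification is used, a second randomisation list. No new measurements, visits or participants are needed, because wells are already tested and baseline samples are already planned.

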### Lentil production and analysis

Small, red, fast-cooking lentils, the preferred kind in Bangladesh, were grown for the trial. Lentils grown in the northwestern USA are low in selenium [18]. In the summer of 2014 a location near Genesee, Idaho was chosen for growing the low-selenium lentils, while the high-selenium lentils were grown at Lucky Lake, Saskatchewan, Canada. All lentils were processed (dehulled, polished, and bagged in colored 25-kg bags) in a lentil dehulling and exporting facility in Vanscoy, Saskatchewan.

Samples of the lentils were analyzed for essential minerals, phytic acid, and macronutrients (Table 2). Idaho lentils contain 0.029 ppm selenium; the Saskatchewan lentils contain 0.854 ppm selenium. The lentils were tested for radiation biosafety certification by the Saskatchewan Research Council, Saskatoon, which declared the two lentil lots fit for human consumption.

**Table 2 Tab2:** Macronutrient and micronutrient content of the two lentil types

Macronutrients	Measure	Sask. lentils	Idaho lentils
Protein	% by weight	26.22	27.73
Starch	% by weight	38.00	37.00
TDF	% by weight	8.48	6.66
Fat	% by weight	0.78	0.77
Ash	% by weight	2.77	3.16
Phytochemicals			
Phytic acid	g/kg	0.61	0.72
Minerals			
Calcium	mg/kg	327.88	377.51
Potassium	g/kg	10.45	10.94
Sodium	mg/kg	71.74	75.00
Magnesium	mg/kg	786.30	943.00
Copper	mg/kg	9.34	11.44
Iron	mg/kg	75.75	65.3
Zinc	mg/kg	42.15	51.9
Manganese	mg/kg	16.95	14.61
Selenium	mg/kg	0.854	0.029
Arsenic	mg/kg	<0.001	<0.001

Abbreviation: *TDF* total digestible fiber

### Lentil shipment and storage

Five metric tons of each lentil type were shipped from Vanscoy, Saskatchewan, to the port in Chittagong, Bangladesh, where they were tested again for radiation and phytotoxins, a protective measure to prevent importation of contaminated grain. Once released the lentils were trucked to icddr,b Dhaka, where each bag was uniquely numbered and stored at room temperature.

### Recruitment

At present, we are recruiting study participants. Two senior field site staff and three village health workers are visiting eligible HHs to obtain consent/assent from adults and children, respectively. The staff will collect sociodemographic data at that time via questionnaire.

### Study procedures

After obtaining consent, families (four to six per week) visit the field office for baseline sample collection and physical examination and for completing the initial morbidity questionnaire. After this first visit, weekly lentil distribution and consumption starts.

The flow chart shows the complete 6-month study procedures (Fig. 1).

**Fig. 1 Fig1:**
[figure not shown]
Flow chart of the dietary intervention trial; BMI, body mass index; BP, blood pressure; HHs, households

At baseline (day 1), midterm (3 months), and at the end of the study (6 months), samples will be collected as described in the following paragraph.

Urine (15–20 ml) will be collected in trace-element free tubes, aliquoted, and stored at –80 °C. Stool samples (5–10 g) will be collected in trace-element free tubes from a subset (about 40) of participants and stored at –20 °C. Blood (10 ml/visit) will be collected in trace-element free tubes (S-Monovette®, Sarstedt). Blood samples, in cool boxes, will be sent to the Dhaka Lab on the same day for separation into plasma and cells, and aliquots of plasma will be stored at –80 °C. Buffy coat cells will be stored in an RNAlater freezer at –80 °C. Whole blood (100 μl) will be stored at –80 °C. Hair will be collected from the back of the head, close to the nape of the neck (approximately 0.2 g) for analysis of arsenic.

Samples may be stored for up to 5 years for future analyses.

The following physical examinations will be performed at baseline, midterm, and end of study:Height and weight are measured to calculate body mass index (BMI).Blood pressure (BP) is tested because of the association between arsenic and hypertension [29].Lung inflammation (NIOX MINO®) — study participants exhale into a machine which detects exhaled nitric oxide, a marker for eosinophilic airway inflammation [30]. Previous reports showed an association of arsenic exposure with respiratory effects and inflammatory response of airway cells [31, 32].

### Laboratory methods

Selenium will be measured in blood by graphite furnace atomic absorption spectrometry (GFAAS). Arsenic in hair, stool, and urine samples will be measured by hydride generation atomic absorption spectrometry (HGAAS) after acid digestion of samples. For determining oxidative stress and antioxidant status, we will measure 8-hydroxy-2'-deoxyguanosine (8-OHdG), a major product of reactive oxygen species (ROS)-induced oxidative stress, in urine/plasma using commercial ELISA kits. Selenium-dependent glutathione peroxidase uses reduced glutathione (GSH) to scavenge ROS, resulting in the production of oxidized GSSG [33]. The antioxidant status (GSH/GSSG) will be assessed with ELISA analysis as described previously [20, 34]. Lipid profiles will be determined in serum by measuring triglyceride, total cholesterol, high-density lipoprotein (HDL), and low-density lipoprotein (LDL) cholesterol using commercial kits from Roche diagnostics on their automated clinical chemistry analyzer Cobas e601 (Roche Diagnostics, Mannheim, Germany). Acute phase response will be determined by analyzing Hs-CRP and α_1_-acid glycoprotein (AGP) in serum using the automated analyzer.

### Data analysis

Data are stored in a password-protected database at icddr,b, through a platform that allows sharing of data between project investigators (PIs) at icddr,b and the University of Calgary. Statistical analyses will be done using the statistical software SPSS for Windows PASW version 20. Normality and homogeneity of variances will be determined. Data not normally distributed will be transformed as necessary. Initially Spearman’s correlation analyses will evaluate univariate association between arsenic exposure (urinary and hair arsenic) and outcome variables (oxidative stress, antioxidant status, lung inflammatory status, and genetic variables). Covariates (e.g., demographic and socioeconomic variables, morbidity, daily diet, and BMI of participants) will be evaluated for significant association with exposure and outcomes. Missing data are excluded from that specific analysis. Significantly correlated variables will be further analyzed in multiple linear regression models controlling for potential confounding variables stratified by sex. Potential confounders will be identified based on correlations (*p* < 0.15) with the exposure (toxic metal) and outcomes and will be included in the final models when they change the effect estimate for metal exposure on the outcome by 5 % or more.

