### Trial objectives

The hypothesis of the trial is that consumption of high-selenium lentils from Saskatchewan, Canada, will reduce the body burden of arsenic and decrease arsenic toxicity in a chronically arsenic-exposed Bangladeshi population compared to those consuming low-selenium lentils.

The primary objective was to perform a double-blind, randomized controlled trial to determine whether incorporation of high-selenium lentils into the daily diet, providing at least the RDA of Se (55 ug), can decrease the body burden of arsenic, evident by higher excretion in urine and/or feces and decreased deposition in hair, compared to the treatment group on low-selenium lentil consumption. Secondary objectives were to determine if consumption of high-selenium lentils:improves antioxidant statusreduces oxidative DNA damagechanges acute phase proteins as well as serum lipid levels in arsenic-exposed individualsdecreases arsenic-related lung inflammation measured using exhaled nitric oxide as an indirect indicatorimproves the body mass index (BMI) and blood pressure of arsenic-exposed individuals

Herein, we describe the design and methods protocol for our 3-year study now underway.

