Key secondary outcomes	We will determine if high-Se lentils:
	1. Increase concentrations of protective antioxidants and reduce oxidative stress and acute phase response in blood
	2. Modulate serum lipid profile and blood pressure
	3. Reduce As-related lung inflammation

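### An unadjusted Spearman screen that ignores lentil group decides which markers are modelled; on 3- or 6-month samples it can lose or invent arsenic–marker associations

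*Protocol article*

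**What the plan says.** The Data analysis section of the protocol article sets out a sequence.

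- The first step is a one-variable-at-a-time screen: "Initially Spearman’s correlation analyses will evaluate univariate association between arsenic exposure (urinary and hair arsenic) and outcome variables". The outcome variables listed are oxidative stress, antioxidant status, lung inflammation and genetic variables.
- The screen decides what follows: "Significantly correlated variables will be further analyzed in multiple linear regression models controlling for potential confounding variables stratified by sex".
- Candidate covariates are an open list: "Covariates (e.g., demographic and socioeconomic variables, morbidity, daily diet, and BMI of participants) will be evaluated for significant association with exposure and outcomes".
- A candidate must correlate with exposure and outcomes at p < 0.15. Candidates "will be included in the final models when they change the effect estimate for metal exposure on the outcome by 5 % or more".

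The section does not mention lentil group in any of these steps. It also does not say which sampling time (day 1, 3 months or 6 months) the correlations use.

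Elsewhere the article expects lentil group to move both sides of these correlations. Under Trial objectives, a lower arsenic burden is to be "evident by higher excretion in urine and/or feces and decreased deposition in hair". In Table 1, the first key secondary outcome is whether high-selenium lentils "Increase concentrations of protective antioxidants and reduce oxidative stress and acute phase response in blood". Lung inflammation is also listed there.

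**The concern.** A variable that moves both arsenic and a marker is a common cause of the two. If it is left out, their correlation contains a part due to that variable alone. On follow-up samples, the trial's own hypotheses give lentil group this role. The Laboratory methods section also describes selenium-dependent glutathione peroxidase, a route from selenium to antioxidant status that need not pass through arsenic.

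The direction depends on the specimen. Suppose higher arsenic goes with more oxidative damage, and the lentils reduce that damage.

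- **Urine.** If the lentils raise urinary arsenic, the two shifts are opposite and the treatment effect cancels the real association.
- **Hair.** If the lentils lower hair arsenic, the shifts agree and the treatment effect adds to the association, or creates one where none exists.

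For a marker that should rise, such as antioxidant status, all signs reverse and the conclusion is the same.

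Cancellation is the firmer harm. A univariate screen cannot adjust for group, and a marker that fails it never reaches the stage where adjustment is possible. Adding a comparison of the lentil groups elsewhere in the plan would leave this screen unchanged.

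**Working it through.** **Inputs from the article.** 200 participants per group, 400 in total (Table 1). Hair arsenic 2.01 (SD 1.4) in controls and 1.23 (SD 0.73) with selenium, one-sided type I error 0.05, power 0.80 (Sample size).

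**Inputs assumed.** Shifts of 0.3, 0.5 and 0.8 within-group SD in both variables; a within-group correlation of 0 or 0.20; independent participants; two-sided 0.05 for the screen. The article gives none of the shifts or correlations.

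**The plan's own figure.** The article states no figure for the correlation step. Its sample size does reproduce: n = (1.4² + 0.73²)(1.645 + 0.842)² / 0.78² = 2.493 × 6.18 / 0.608 = 25.3, so 26 per group as stated. The same inputs give the hair difference in SD units: 0.78 / √(2.493/2) = 0.78/1.116 = 0.70 SD. This serves only as a scale for what follows.

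**Correlation when group is ignored.** With two equal groups, within-group correlation r, and shifts dA (arsenic) and dY (marker) in within-group SD:

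r_all = (r + dA·dY/4) / √[(1 + dA²/4)(1 + dY²/4)]

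*Opposite shifts, r = 0.20 (the urine case):*

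| dA / dY | r_all | Screen power (simulated Spearman) |
|---|---|---|
| 0 / 0 | 0.20 | about 97% |
| +0.3 / −0.3 | (0.20 − 0.0225)/1.0225 = 0.174 | about 90% |
| +0.5 / −0.5 | (0.20 − 0.0625)/1.0625 = 0.129 | 69% |
| +0.8 / −0.8 | (0.20 − 0.16)/1.16 = 0.034 | 7% |

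Ranking within group keeps power at about 97% in the 0.5 and 0.8 SD rows.

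*Same-direction shifts, r = 0 (the hair case):*

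| dA / dY | r_all | Screen rejects a true null |
|---|---|---|
| −0.3 / −0.3 | 0.0225/1.0225 = 0.022 | about 7% |
| −0.5 / −0.5 | 0.0625/1.0625 = 0.059 | about 21% |
| −0.8 / −0.8 | 0.16/1.16 = 0.138 | about 80% |

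Ranking within group returns the rejection rate to about 5%.

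**Effect of the plan's confounder rule.** The r = 0 cases were rerun with lentil group offered as a candidate under the p < 0.15 and 5% rule. Group entered in 86% to 100% of runs, and false positives that survived both the screen and the final model were 2% to 3%. So 7%, 21% and 80% describe the screen, and they carry into the final model only if group is not a candidate. The rule cannot help a marker that has already failed the screen.

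**Sensitivity to size.**

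- If only one variable shifts, little changes: with r = 0.20, no urine shift and a marker shift of −0.5 SD, power is still 96%. With r = 0 and only arsenic shifted, the rejection rate stays at 5%.
- With the hair shift at 0.70 SD and marker shifts of −0.20 to −0.70 SD, the null rejection rate is 10% to 59%. At half the hair shift (0.35 SD) it is 6% to 21%. At a quarter (0.17 SD) it is 5% to 9%.

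**The case against.** The strongest reply is that much of this is read from silence. The section never says the groups are pooled, and it fixes no sampling time. It calls urinary and hair arsenic an exposure and lists genetic variables among the outcomes, which fits an association analysis of day-1 samples, where no treatment effect can exist. That reading is open, and on it the problem disappears. A condensed article may also leave model terms to the full plan. What stands is the sequence the article does fix: a univariate screen that decides what is modelled. No later choice of covariates repairs that on follow-up data.

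A reader might infer that the plan will report a hair-arsenic effect that does not exist. The article does not support this. The covariate list is open and includes daily diet, so lentil group could be a candidate, and the plan's rule would then remove the spurious result in nearly every affected run.

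A reader might also infer that cancellation in urine is expected. The objective says urine and/or feces, and the Background says the selenium–arsenic complex is excreted in bile, so a urinary shift is not certain.

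The shifts may be small. The 0.70 SD comes from a trial with two to four times the selenium, over 9 months rather than 6, and it concerns hair only. The Discussion itself expects that some biomarkers may not differ between groups. This is fair, and the size is conditional on it.

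Finally, if selenium improves a marker by lowering arsenic, part of the between-group association is a real arsenic effect and not bias. That is correct, and it limits how a group-adjusted estimate may be read. The glutathione peroxidase route shows why the whole of it should not be assumed real; that route concerns antioxidant status and does not extend to lung inflammation.

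**Conclusion.** The point holds conditionally. On 3- or 6-month samples, if the lentils shift both arsenic and a marker, the screen as written tests a mixture of treatment effect and arsenic–marker association. The firm consequence is at the gate: a real association can be cancelled and the marker then receives no adjusted model. The loss is modest at 0.3 SD, material at 0.5 SD and nearly complete at 0.8 SD. Inflated false positives are certain only for the screen; whether they reach the final model depends on whether lentil group is a candidate, which is not stated.

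The figures rest on assumed shifts and correlations, independent participants and 400 complete pairs. The article does not support the stronger claims that pooling is prescribed or that biased results are inevitable. These are also supporting analyses, since every stated objective concerns the effect of lentil type. The change is still worth making because the distortion grows with the treatment effect.

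**What to change.** In Data analysis:

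1. State the sampling time. Either run the arsenic–marker correlations and regressions on day-1 samples only, or, for 3- and 6-month samples, always include lentil group (partial Spearman correlation, or a group term in the regression) without subjecting it to the p < 0.15 and 5% rule.
2. Do not let the unadjusted correlation decide which listed outcome variables are modelled; fit the model for each of them.
3. Label these analyses exploratory, and note that the group-adjusted estimate excludes any effect of the lentils that acts through arsenic.

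The cost is a few sentences, one degree of freedom for the group term and a few more models. The day-1 option instead gives up the follow-up samples for this analysis. No new data are needed, and the article reports recruitment as still under way.
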